### Sample size estimation

Sample size of the planned project is based on an a priori power analysis. With 52 participants completing the group BPT (study site Basel: *n* = 26, study site Winterthur: *n* = 26), we will have sufficient power (1-*β* = 0.94) to gain pre-post differences of medium effect size (*d* = 0.5) in the primary outcome. Allowing for a 30% dropout rate and including a safety margin of 10% accounting for unexpected variation in our estimates, we aim to include a total of *N* = 88 patients. With regard to the nested RCT evaluating the short-term efficacy of smartphone-triggered bodily interventions, power analysis is more demanding. Given a maximum of 15 bodily interventions and 15 control interventions per person and assuming a participation rate in daily interventions of 80% (which is a rather conservative estimate, as compared to the previously observed 96% participation rate in an earlier study [51]), we expect on average a total of 24 completed smartphone-triggered interventions per participant. Assuming a correlation of 0.5 among repeated measures and a nonsphericity correction ε of 1, we expect sufficient power (1-*β* > 0.99) to detect medium effect sizes (*f* = 0.25) (estimation conducted using G*Power 3.1 [69], based on an analysis of variance (ANOVA) model with repeated measures and within factors).

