### Interventions

#### Group BPT intervention

The first author developed the intervention based on integrative body psychotherapy approaches [20, 28, 29], adapted to cancer patients and their needs and opted for group setting. Compared to individual therapy, group interventions may benefit from additional therapeutic factors and may have economic benefits [49, 50]. First experiences with group BPT for cancer patients were obtained from an initial group (6 patients), as described elsewhere [25]. The intervention is carried out in small groups within 6 sessions, 90 min each. The intended time frame for conducting all 6 sessions is 6–8 weeks (public holidays etc. included). The group BPT is provided as part of the outpatient service of University Hospital Basel and Cantonal Hospital Winterthur, using facilities from the Cancer Leagues Basel and Zürich in close proximity to the hospitals.

The 6 group BPT sessions will comprise the following topics: 1) general introduction, fostering of group cohesion and focus on bodily perception; 2) focus on bodily resources and grounding; 3) focus on closeness and distance regulation; 4) focus on social interactions and bodily impulses; 5) focus on embodied emotions; and 6) summary and transfer session. All sessions should proceed along the following phases: A) Opening: brief bodily exercise and exchange, preparing the specific topic of the session; B) Psycho-educational element and exercises triggering embodied experiences, focusing on the specific topic of the session with sharing (reflection and exchange of experiences during the exercise); C) Closure: résumé and farewell (see Table 2 and Grossert et al. [25]). Within this schedule, each session can be adapted to the composition of the current patient group and its respective needs. Thus, group processes can be addressed accordingly. In between sessions, patients are instructed to continue the exercises (supported by smartphone-based triggers, see below), making sure that tools, experiences, and strategies are transferred and integrated into their daily lives. To improve intervention adherence, participants are contacted, if they do not attend a group appointment without having given prior notice. Patients are informed that they can contact us at any time if they have any uncertainties or questions.

**Table 2 Tab2:** Content of interventions: Group body psychotherapy with cancer patients and smartphone based bodily interventions

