4.	Impulses and social/group interaction	▪ Short body scan CEB ▪ Lika breathing technique, p37 [45] ▪ Feedback	1) Social interactions and (body) impulses to get into/out of social interactions 2) – Body self-release techniques, adapted p209 [28] - Awareness of bodily perception and the nature of impulses - nonverbal contact Interaction with different body parts 3) Reflection about own experience during the exercises	How can I find a witness position being aware of perception and impulses? What do I need?	Relaxation through body self-release techniques
5.	Embodied emotions	▪ Short body scan CEB ▪ Anchoring exercise ▪ Feedback	1) Integration model of human experience, p26 [28] 2) - Mapping of feelings under the cancer disease and treatment - Focus on embodiment: body sculptures of emotions, adapted [46] 3) Reflection about own experience during the exercises	How to become aware of feelings and how to explore and share them in daily life?	Self-awareness through ‘four body zone’ exercise
6.	Summary	▪ Short body scan CEB ▪ Free choice of exercise repetition ▪ Feedback	1) Summary and open questions 2) Free choice of exercise repetition 3) Closing: Ritual “*being connected while continue on individual path*”	What would I take with me? What would I leave in this group/room? Evaluation	

*BPT* Body Psychotherapy, *CEB* Cognition, emotions, body perception

Group BPT is provided by three trained psychotherapists. In order to guarantee continuity within each group, one single therapist leads all 6 sessions of a specific group. Therapists have a professional background in terms of either a medical or psychological degree, followed by specialized training in integrative body psychotherapy (IBP; accredited by the Federation of Swiss Psychologists). Furthermore, they then receive training in the ‘group BPT for post-treatment cancer patients’ approach by the first author of the present study according to the specific manual which describes the group content in detail (manual not yet published, for an outline see Table 2.). At the beginning and end of completing a series of the six BPT session, mandatory peer consulting of the therapy is provided by the first author and then continuously ensured according to the needs of the group leader. In case the first author is conducting the group, continuous supervision of the therapy is provided by a senior body psychotherapist.

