### Statistical and content analyses

Descriptive analyses of continuous variables will include the calculation of central tendency and dispersion; descriptive analyses of categorical variables will include numbers and frequencies.

We intend to use inferential statistics to compare outcomes and parameters over time: (1) from baseline to post group BPT intervention and (2) from pre to post smartphone-triggered bodily intervention. We intend to compare changes from T1 to T2 with changes from T0 to T1. Therefore, we intend to use mixed effect generalized linear models, which will also be used to assess potential mediators of therapeutic changes. Baseline equivalence between T0 and T1 will be assessed in order to adjust potential baseline differences and that way to reduce potential bias arising from the nonrandomized study design. We intend to conduct additional analyses, including adjusted (e.g., age, gender) and subgroup analyses (e.g., cancer entity, BPT group composition, level of somatic distress). All statistical tests will be two-sided, and *p*-values ≤0.05 will be considered statistically significant. In the event of multiple comparisons, Bonferroni-Holm corrections will be carried out.

We intend to analyze qualitative data based on thematic analyses, aiming at identifying themes within the data and at establishing meaningful categories, their interrelation, and their relation to the outcomes of the intervention [68, 70].

Intention-to-treat analyses will include all patients being enrolled in the study and randomized. Per protocol analyses will follow an all-patients-receiving-intervention perspective. Whenever appropriate, we are going to use multiple imputation methods [71].

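### The stated power of 0.94 treats 52 participants as independent and makes no allowance for treatment in small therapy groups

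*Protocol article*

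**What the plan says.** The section on sample size estimation bases its power statement on completers: "With 52 participants completing the group BPT", 26 at each of two sites, the trial is said to have power 0.94 "to gain pre-post differences of medium effect size" (d = 0.5) in the primary outcome. Enrolment is then raised to 88: "Allowing for a 30% dropout rate and including a safety margin of 10% accounting for unexpected variation in our estimates". The section gives no group size, number of groups, ICC or design effect.

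The section on the group BPT intervention describes delivery: "The intervention is carried out in small groups within 6 sessions, 90 min each". Three therapists serve the trial, and "one single therapist leads all 6 sessions of a specific group". The same section gives the extra therapeutic factors of a group as one reason for the format, and lets each session be adapted to the group's composition. Group cohesion is measured after every session, and assessing it is a secondary objective.

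For the analysis, the article says "we intend to use mixed effect generalized linear models" to compare the T1-T2 change with the T0-T1 change. It lists no random effects. The composition of the therapy group appears only as an example of a subgroup factor. On testing it states: "All statistical tests will be two-sided", at the 0.05 level.

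**The concern.** Members of one therapy group share a therapist, the sessions and each other, and the protocol itself expects group processes to contribute to benefit. Their changes from T1 to T2 may therefore be correlated. With positive correlation, the mean change is estimated less precisely than 52 independent people would allow, and the number of groups limits the information about between-group variation.

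Comparing the BPT phase with the waiting period does not remove the problem. Groups act only in the BPT phase, so a group effect on the T1-T2 change does not cancel against T0-T1.

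At stake is the reliability of a printed planning figure for the primary outcome. The validity of the final test is affected only if the analysis model leaves group out.

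**Working it through.** **Inputs from the article.** 52 completers; d = 0.5; two-sided alpha 0.05; stated power 0.94; 88 enrolled; 30% dropout. The only group size given is 6, for one group run before the trial.

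**Assumptions (not in the article).** ICC of the T1-T2 change 0.02, 0.05 or 0.10. Two layouts:
- A: six completers per group, 52/6 = 8.67 groups.
- B: groups of six formed from all 88 enrolled, 88/6 = 14.67 groups (about 15), so 52/14.67 = 3.55 completers per group.

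**Step 1: reproduce the stated figure.** Paired t-test on 52 independent change scores: noncentrality 0.5 × √52 = 3.606, df = 51, power 0.943. This matches 0.94, so the figure contains no allowance for groups.

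**Step 2: allow for groups.** With m completers per group:
- design effect DE = 1 + (m − 1) × ICC
- effective n = 52/DE
- noncentrality = 0.5 × √(effective n)
- df = number of groups − 1 (cautious), or 51 (lenient)

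| Layout | ICC | DE | Effective n | Power, group-based df | Power, df 51 |
|---|---|---|---|---|---|
| A | 0.02 | 1.10 | 47.3 | 0.85 | 0.92 |
| A | 0.05 | 1.25 | 41.6 | 0.80 | 0.89 |
| A | 0.10 | 1.50 | 34.7 | 0.73 | 0.82 |
| B | 0.02 | 1.05 | 49.5 | 0.90 | 0.93 |
| B | 0.05 | 1.13 | 46.1 | 0.88 | 0.92 |
| B | 0.10 | 1.25 | 41.4 | 0.85 | 0.89 |

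Group-based df are 7.67 in layout A and 13.67 in layout B. Part of the loss in that column comes from the df alone: in layout A it gives 0.88 even at ICC 0. With df 51 and ICC 0.01, power is 0.93 in layout A, which hardly differs from 0.94.

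**Step 3: type I error if, and only if, group is left out of the final model.** The approximation is 2 × [1 − Φ(1.96/√DE)]:
- layout A: 0.062, 0.080, 0.110
- layout B: 0.056, 0.065, 0.080

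**Step 4: completers needed to keep an effective n of 52 at six per group.** 52 × 1.25 = 65 at ICC 0.05; 52 × 1.50 = 78 at ICC 0.10.

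**Step 5: use the enrolment margin.** If dropout is exactly 30%, 88 × 0.70 = 61.6 complete. Power for ICC 0.02, 0.05 and 0.10 is then 0.92, 0.88 and 0.82 with group-based df at six completers per group, and 0.94, 0.92 and 0.89 with 15 groups.

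**The case against.** **The analysis may already handle groups.** This stands. The article plans mixed models and names no random effects, not even participant. A condensed article commonly leaves such detail to the full plan. A reader might infer that clustering is ignored in the analysis and that the test is therefore invalid. The article does not support that inference, so the error rates in Step 3 are conditional.

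**The number of groups and the ICC are unknown.** This also stands. A reader might divide 52 by a size of five to eight and take about 7 to 10 groups as given. The article gives no such number, and groups formed from the 88 enrolled could number about 15, with a smaller loss. Nothing in the article supports a particular ICC for change in the Body Image Scale. Measuring cohesion does not show that the correlation is large.

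**Enrolment has slack.** In part. With 61.6 completers, power stays above 0.80 over the whole assumed ICC range at six per group. But the 10% margin is for unexpected variation in the estimates and is not linked to grouping. The 0.94 is computed at 52 completers, so the margin does not rescue that figure.

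**Conclusion.** The point holds for the planning figure. The printed 0.94 is the power for 52 independent paired differences, and it is too high for any positive within-group correlation of the T1-T2 change.

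How far too high depends on quantities the article does not give. The range in Step 2 runs from 0.93 (about 15 groups, ICC 0.02, df 51) down to 0.73 (six completers per group, ICC 0.10, group-based df). At a very low ICC with df 51 the loss is trivial.

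Two stronger readings are not supported. The trial cannot be called underpowered, because most of the scenarios examined stay at or above 0.80. Nor can the type I error be called inflated: it would be about 0.06 to 0.11 only if the final model omitted therapy group. The two statements are linked, however. A model that accounts for group does not reach 0.94 when the ICC is positive, and a model that omits it does not hold the 5% level.

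**What to change.** State the planned group size and number of groups, and replace the single 0.94 with power over a stated range of group sizes and ICCs, as in the table above. In the primary mixed model, include therapy group as a random effect on the BPT-phase (T1-T2) change, since groups do not act during the waiting period. Use a small-sample df correction such as Kenward-Roger or Satterthwaite. If the full analysis plan already contains this term, only the power statement needs to change.

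The cost is wording, somewhat wider intervals and a less favourable stated power. No new data are needed, because each participant's therapy group is known from delivery.

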### Statistical and content analyses

Descriptive analyses of continuous variables will include the calculation of central tendency and dispersion; descriptive analyses of categorical variables will include numbers and frequencies.

We intend to use inferential statistics to compare outcomes and parameters over time: (1) from baseline to post group BPT intervention and (2) from pre to post smartphone-triggered bodily intervention. We intend to compare changes from T1 to T2 with changes from T0 to T1. Therefore, we intend to use mixed effect generalized linear models, which will also be used to assess potential mediators of therapeutic changes. Baseline equivalence between T0 and T1 will be assessed in order to adjust potential baseline differences and that way to reduce potential bias arising from the nonrandomized study design. We intend to conduct additional analyses, including adjusted (e.g., age, gender) and subgroup analyses (e.g., cancer entity, BPT group composition, level of somatic distress). All statistical tests will be two-sided, and *p*-values ≤0.05 will be considered statistically significant. In the event of multiple comparisons, Bonferroni-Holm corrections will be carried out.

We intend to analyze qualitative data based on thematic analyses, aiming at identifying themes within the data and at establishing meaningful categories, their interrelation, and their relation to the outcomes of the intervention [68, 70].

Intention-to-treat analyses will include all patients being enrolled in the study and randomized. Per protocol analyses will follow an all-patients-receiving-intervention perspective. Whenever appropriate, we are going to use multiple imputation methods [71].

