**Methods:**

The project is a bi-center study with two participating centers in Switzerland, applying a pre-post convergent parallel design of a weekly group BPT using a waiting-period comparator, including a nested RCT during the group BPT phase. During the BPT phase, either a smartphone-triggered bodily intervention or a smartphone-triggered control intervention is provided at random over 5 consecutive weeks, on 6 days weekly. Patients who had received curatively intended treatment for any malignant neoplasm (treatment being completed ≥3 months) and are suffering from bodily disturbances are screened to assess eligibility. Sample size estimation is based on an a priori power analysis. We plan to include a total of *N* = 88 subjects, aiming at at least 52 completers.

Patients are surveyed three times (baseline assessment (T0), pre- (T1) and post-intervention assessment (T2)), and on a daily basis along BPT during five consecutive weeks. The primary outcome, bodily disturbances, is assessed using the ‘Body Image Scale‘(BIS). For the secondary outcomes standardized questionnaires are used to assess changes in experience of presence and vitality, mood, body mindfulness, somatic symptoms and somatic symptom disorder, quality of life, anxiety, and depression including suicidal tendency, vitality and mental health, as well as group cohesion. Using semi standardized interviews (at T0 and T2), we aim to explore the relation of BPT with bodily disturbances and body image in post-treatment cancer patients, as well as the acceptance and burden of the intervention.

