### Study aims and objectives

The aims of this trial are to evaluate whether bodily disturbances in post-treatment cancer patients can be improved by group BPT, and to estimate the efficacy of intermittent smartphone-triggered bodily interventions (German acronym ‘KPTK: **K**örper**p**sycho**t**herapie bei **K**rebs’ in English: BPT for cancer patients. For trial registration data see Additional file 1). We assume that bodily disturbances will improve from pre- to post-BPT in post-treatment cancer patients. Furthermore, participants will show better immediate outcomes with regard to mood and bodily well-being if they receive smartphone-triggered bodily interventions as compared to smartphone-triggered control interventions. With this non-randomized evaluation of a weekly group BPT using a waiting-period comparator, with a nested randomized controlled trial (RCT) we will primarily obtain information on the efficacy of the intervention. Furthermore, we will be able to investigate intervention effects and mechanisms of action in more detail, together with acceptance and perception of the intervention, unwanted effects and burden to patients.

The primary objective of the planned project is to evaluate whether group BPT is related to reduction of bodily disturbances in post-treatment cancer patients.

Secondary objectives of the project are
to assess if BPT is related to more body awareness/mindfulness;to estimate, whether intermittent smartphone-triggered bodily interventions go along with immediate improvements in bodily well-beingto evaluate, whether BPT is related to improvements in mental well-being (anxiety, depression, somatization, pain, etc.) and quality of life;to assess group processes/cohesion;to assess aspects of the intervention, such as
recruitment and inclusion;undesired side effects (‘safety assessment’);from the patients’ perspectives:
(i)acceptance and burden of the intervention (this assessment is recommended according to recent initiatives, such as ‘Partnering with Patients’ launched by the British Medical Journal (BMJ) [37]);(ii)suggestions for improvement of the intervention.

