### Study sample

We intend to include a total of 88 patients (44 at each study side). With an expected response rate of approximately 70%, we aim at a sample size of 52 completers (26 per participating center). The therapeutic intervention provided in this study aims at post-treatment cancer patients suffering from disturbances in bodily well-being. Patients having received curatively intended treatment for malignant neoplasms at the participating institutions, are screened according to the eligibility and exclusion criteria outlined in Table 1.

**Table 1 Tab1:** Inclusion and exclusion criteria

*Inclusion criteria:*	
• Having received curatively intended treatment for any malignant neoplasm;	
• Primary treatment (surgery, radiotherapy, chemotherapy) being completed ≥3 months ago before study inclusion. Any other ongoing anti-tumor therapy is allowed (e.g., hormonal therapy, adjuvant immunotherapy);	
• Bodily disturbances (BIS ≥10) (= clinical cutoff for body image dissatisfaction [9]); OR ((BIS = 2–9) AND ((patient-assessed distress due to bodily changes (VAS-B; 0–10) ≥ 5) OR (therapist-assessed awareness of bodily changes (VAS-A) ≥ 5 AND therapist-assessed related distress due to bodily changes (VAS-B, 0–10) ≥ 5)))	
• No sign of progress or recurrence of malignancy at study inclusion according to treating physician;	
• Score of 0 or 1 according to the PS of the ECOG [41];	
• Having an anticipated life expectancy of ≥12 months, according to treating physician (recent evidence suggests that this is the best source for prediction of survival [42]);	
• Age 18 years or older;	
• Capacity to participate in group BPT sessions in Basel or Winterthur, 3 study assessments, and the smartphone-triggered interventions;	
• Ability to provide informed consent.	
*Exclusion criteria:*	
• Suffering from a severe current mental disorder;	
• Risk of current suicidality, as indicated by a suicide item score ≥ 2 in the BDI-II [43], as this group BPT intervention is not appropriate to support suicidal patients in acute crises. (Given a score ≥ 2, need for support will be assessed and if required, patients are instructed to call for or transferred to local psychiatric support);	
• Participation in any other clinical trial with a psychosocial intervention;	
• Receiving any other current psychotherapeutic treatment with the exception of already existing long-lasting therapies (≥ 6 months);	
• Inability to understand and speak German.	

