### Recruitment and screening

Recruitment takes place at University Hospital Basel and at the Cantonal Hospital Winterthur. Further, potential participants are approached via public advertisements (e.g. advertisement in public transport and on the website of the Basel Cancer League). Patients having received curatively intended treatment for any malignant neoplasm (treatment being completed ≥3 months) and suffering from bodily disturbances due to the cancer diagnosis and treatment are provided with oral and written information about the study and asked if they are willing to participate. Patients are informed by trained research nurses or the project leader. In addition, the date and time of the specific BPT group are clarified with each participant in advance. Once written informed consent has been obtained, patients are screened with baseline assessment (T0), including standardized questionnaires and a semi-structured baseline interview whether they are eligible for the BPT intervention or not. Non-eligible patients are provided with information regarding alternative therapeutic support. Included patients undergo a waiting period of 6 weeks (given that recruitment for a group intervention is difficult, reasonable exceptions of a shorter waiting period are allowed) followed by the pre-intervention assessment (T1), weekly assessments after each group BPT session, and daily pre−/post smartphone-triggered assessments. After completion of the group BPT phase, the post-intervention assessment (T2) with standardized questionnaires and a semi-structured post-intervention interview takes place (Table 3 gives an overview of assessment instruments and time points).

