### Assessments

For all assessments, we apply validated instruments with good quality criteria. Sociodemographic variables are assessed at baseline (T0) only. All other constructs are assessed three times: at baseline after study enrollment (baseline assessment; T0), after the waiting period (pre-intervention assessment; T1), and after completion of the group BPT (post-intervention assessment; T2).

Within the group intervention, bodily disturbances, body mindfulness and group cohesion is evaluated weekly after each group BPT session. Experience of presence and experience of vitality and mood are additionally assessed pre- and post-smartphone-triggered interventions. Furthermore, therapist’s adherence to the manual is recorded with a respective checklist adapted to the session’s context. Table 3 gives an overview of outcome measures, assessment instruments, and time points.

**Table 3 Tab3:** Outcome measures, assessment instruments, and assessment time points

Measures	Assessment instruments	Baseline Assessment T0	Pre-Intervention Assessment T1	Weekly assessments after group BPT	Pre/Post smartphone-triggered intervention	Post-Intervention Assessment T2
Social demographics	Sociodemographic variables (sex, age, marital status, educational level, and job-related situation)	X				
Psychosocial health	Basic Documentation for Psycho-Oncology (PO-Bado)	X				
Performance status	Performance status score of the Eastern Cooperative Oncology Group (ECOG)	X				
Bodily disturbances	Body Image Scale (BIS)	X	X	X		X
Awareness of bodily changes due to the diagnosis and treatment	single item; VAS-A patient-assessed (range 0–10)	X	X			X
Distress caused by bodily changes	single item; VAS-B patient-assessed (range 0–10)	X	X			X
Body mindfulness	Body Mindfulness Questionnaire (BMQ)	X	X	X		X
Distress	National Comprehensive Cancer Network Distress Thermometer (DT)	X	X		X	X
Somatic Symptoms	Somatic Symptom Disorder-B Criteria Scale (SSD-12)	X	X			X
Quality of life	EORTC QLQ-C30	X	X			X
Vitality	36-Item Short Form Health Survey (SF-36) – Scale Vitality	X	X			X
Mental health	36-Item Short Form Health Survey (SF-36) – Scale Mental Health	X	X			X
Anxiety and depression	Hospital Anxiety and Depression Scale (HADS)	X	X			X
Suicidal tendency	Beck Depression Inventory (BDI-II), Item I: Suicidal tendency	X	X			X
Group cohesion	Group Climate Questionnaire – Short Form (GCQ-S)			X		X
Mood	Multidimensional Mood Questionnaire (MDMQ)				X	

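### The first listed group-BPT comparison starts at T0 rather than T1, so it includes the untreated waiting period and regression from the screening BIS

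*Protocol article*

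**What the plan says.** **The comparison.** The section on statistical and content analyses lists two inferential comparisons over time. The one for the group therapy is "1) from baseline to post group BPT intervention". The sentence after it plans to set the change from T1 to T2 against the change from T0 to T1, using mixed models. A check of T0 against T1 follows, as a basis for adjustment.

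**The time points.** The abstract names them as "baseline assessment (T0), pre- (T1) and post-intervention assessment (T2"). The Assessments section places them as "at baseline after study enrollment (baseline assessment; T0), after the waiting period (pre-intervention assessment; T1"). Between T0 and T1, "Included patients undergo a waiting period of 6 weeks", with shorter waits allowed in some cases.

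**The hypothesis.** Under study aims: "We assume that bodily disturbances will improve from pre- to post-BPT in post-treatment cancer patients". The sample size section is also framed as a pre-post difference: 52 completers, d = 0.5, power 0.94.

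**Selection.** Under recruitment, "patients are screened with baseline assessment (T0), including standardized questionnaires". Table 1 admits patients with "Bodily disturbances (BIS ≥10"), or with BIS 2 to 9 plus patient- or therapist-rated VAS criteria. The BIS is also the primary outcome.

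**The concern.** By the article's own terms, the listed comparison (T0 to T2) is not the one the hypothesis and the power statement describe (T1 to T2). The difference matters for two reasons.

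- The T0-T2 change contains whatever happens while patients wait untreated. The length of that wait may also differ between patients.
- T0 is the measurement on which patients are admitted. When entry depends on a high score, the mean is expected to fall at re-measurement even if nothing is done. T1 is not used for selection, so a change measured from T1 is largely free of this.

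A significant T0-T2 result would therefore not by itself be evidence that BPT reduces bodily disturbances. The planned Bonferroni-Holm correction deals with the number of tests and does not remove a bias within one of them.

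**Working it through.** **1. The plan's own figure.** Inputs from the sample size and statistical sections: n = 52, d = 0.5, two-sided alpha 0.05. For a paired t-test with 51 degrees of freedom the noncentrality is 0.5 × √52 = 3.61, which gives power 0.943. The stated 0.94 is reproduced. It belongs to one pre-post change.

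**2. What T0-T2 contains.** (T2 − T0) = (T1 − T0) + (T2 − T1). With no BPT effect the second term has mean zero, and any waiting-period change passes in full into the T0-T2 test. Let dz be that untreated shift divided by the standard deviation of the T0-T2 change. The probability of a significant result at n = 52 is then:

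| Untreated shift dz | dz × √52 | P(significant T0-T2) |
|---|---|---|
| 0 | 0 | 0.05 |
| 0.1 | 0.72 | 0.11 |
| 0.2 | 1.44 | 0.29 |
| 0.3 | 2.16 | 0.56 |
| 0.4 | 2.88 | 0.81 |

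**3. Regression to the mean alone.** The documents give no BIS mean, standard deviation or retest correlation, so these are assumptions. For normal scores with retest correlation r and entry above a cut c (in SD units from the source mean), the expected fall is (1 − r) × φ(c) / (1 − Φ(c)).

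- Example with r = 0.8 and c = 0: 0.2 × 0.798 = 0.160 SD. The variance of the change among those selected is 0.2² × 0.363 + (1 − 0.8²) = 0.375, so its SD is 0.612. Hence dz = 0.160 / 0.612 = 0.26 and the false-positive rate is about 0.46.
- Over r = 0.7 to 0.9 and c = −1 to +0.5: fall 0.03 to 0.34 SD, dz 0.07 to 0.47, false-positive rate 0.07 to 0.91.

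**4. Allowing for the second entry route.** Simulation with BIS rounded and limited to 0-30, source SD 6, three equally correlated measurements, selection on T0, n = 52 and no BPT effect:

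| Source mean | r | Share of BIS 2-9 scorers admitted | P(significant T0-T2) |
|---|---|---|---|
| 8-10 | 0.7-0.9 | none | about 25-79% |
| 8-10 | 0.7-0.9 | 30% | about 13-42% |
| 8-10 | 0.7-0.9 | 60% | about 9-20% |
| 14 | 0.8 | none to 30% | about 10-17% |

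In the settings with source mean 8-10, T1-T2 rejected in about 5% of trials, as it should. That result relies on equal correlations. If correlation decays with time, a little regression would carry over into T1-T2.

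**5. The change-versus-change comparison.** The contrast (T2 − T1) − (T1 − T0) equals T2 − 2·T1 + T0.

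- *Power.* Under compound symmetry its variance is 6(1 − r) (unit-variance scores), against 2(1 − r) for a single change, so its SD is √3 times larger. With no waiting-period change, d = 0.5 becomes 0.5 / √3 = 0.289, and power at n = 52 is 0.53. Under AR(1) with r = 0.5 to 0.8 it is 0.61 to 0.66. Power of 0.94 under compound symmetry would need about 151 completers.
- *Bias.* Regression from T0 makes T1 − T0 negative. The contrast subtracts that term, so it moves against BPT by the same number of points. Example with source mean 8, SD 6, r = 0.8 and all patients at BIS 10 or above: T2 − T0 = −1.17 points and contrast = +1.20 with no effect. In that setting a true d = 0.5 is detected in only about 12-13% of trials, and about 24% of null trials reject against BPT.

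**The case against.** The strongest reply is that items (1) and (2) only separate the group therapy from the smartphone component and do not rank tests. The sentence that follows ties the mixed model to T1-T2 change against T0-T1 change. That is the waiting-period comparator the design is built on, and it removes the untreated change from the estimate apart from the regression bias. Baseline is also used loosely in the same section, where T0 and T1 are to be checked for baseline equivalence. Item (1) may simply mean the whole span of assessments.

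Much of this stands. A reader might infer that the trial's main conclusion will rest on T0 to T2. The document does not say so, and it plans a better comparison in the next sentence. It is also no finding that the article leaves the deciding contrast unnamed, since the full protocol or analysis plan may name it.

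What does not fall is the wording. Every definition of baseline in the article is T0. If T1 was meant, the item needs the same correction.

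The objection to the size also has force. A reader might take the upper rates, near 80% or above, as the trial's false-positive rate. They need assumed BIS values and all or most patients entering above a single cut. Table 1 admits BIS 2 to 9 as well, and recruitment targets people already suffering from bodily disturbances, so the screened mean may lie well above 10.

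**Conclusion.** The point holds as a mismatch with a known direction of bias. Item (1), read by the article's definitions, is T0 to T2. It does not match the pre- to post-BPT hypothesis or the power statement, and it can show improvement without any BPT effect.

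The size cannot be fixed from the documents. At n = 52 the false-positive rate is about 11% to 81% for an untreated shift of dz 0.1 to 0.4. It lies toward the low end if many patients enter with BIS 2 to 9 or if the screened mean is well above 10. The planned change-versus-change comparison limits the damage but does not remove the T0-T2 test.

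A reader might also infer that this contrast should become the single deciding test. The present sample size statement does not support that. The stated 0.94 is for one pre-post change, and the contrast has about 0.53 for the same effect before any regression to the mean. Calling it merely conservative would understate the problem, because selection on the T0 BIS can push it to significance against BPT.

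**What to change.** - Change item (1) to T1 to T2. The stated power of 0.94 (n = 52, d = 0.5) applies to that comparison.
- Report T0 to T2 descriptively only.
- Keep the comparison of T1-T2 change with T0-T1 change as the waiting-period-controlled analysis. State beside it that the 0.94 does not apply (about 0.53 for the same effect under compound symmetry with no waiting-period change), and that regression to the mean from selection on the T0 BIS biases it against BPT.
- Do not make that contrast the sole deciding test on the present sample size statement. That would need its own power calculation, and about 151 completers for 0.94 under the assumptions above.

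The first three changes are wording only. They need no new data and no larger sample. The reported headline change may be smaller than a T0-T2 figure would have been.
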